### Ethical Considerations

The study was approved by the Swedish Ethical Review Authority (registration 2020–03198; 2023–06857-02) and was preregistered on ClinicalTrials.gov (NCT04797273). All participants provided written informed consent before inclusion, and their data are pseudonymized and securely stored on an encrypted server. Participants received no monetary compensation but accessed study interventions free of charge. No identifying information of participants will be included in the manuscript or supplementary materials.

### Procedure

#### Participants

In total, 300 nationally recruited individuals were diagnosed with a primary diagnosis of AD (n=142, 47.3%) or ED (n=158, 52.7%) and were included in the RCT. Participant recruitment was carried out through social media, newspaper advertisements, and information provided to health care clinics. Participants self-referred to the study web page, where they signed digital informed consent and completed a screening battery consisting of sociodemographic and clinical background questions as well as self-report symptom questionnaires. Participants were subsequently clinically assessed by a psychologist using a structured diagnostic interview, including Mini International Neuropsychiatric Interview [31], self-rated ED [32], and the Adjustment Disorder New Module-8 (ADNM-8) [33]. For inclusion, participants needed to (1) fulfill the criteria for a primary diagnosis of AD or ED, (2) be aged between 18 and 65 years, (3) have regular access to a computer with internet access, and (4) be able to read and write in the Swedish language. Exclusion criteria included (1) drug use or addiction during the past 6 months, (2) current or past psychosis or bipolar disorder, (3) current risk of suicide, (4) changed psychopharmacological treatment in the past month, (5) other ongoing psychological treatment, and (6) previous experience of CBT for AD or ED in the past year.

#### Treatment

Patients were randomized to one out of two 12-week internet-delivered treatments (CBT and general health-promoting advice). They both consisted of web-based text-based modules with related exercises and assignments. Patients were guided sequentially through the modules by a therapist via a secure web-based platform. The therapists’ primary role was to provide feedback on exercises, support in problem-solving, and to give emotional and technical support via weekly asynchronous text messages. Therapists were licensed clinical psychologists or clinical psychology students in their final year of training. Because this study will not evaluate the individual treatments, they will not be further described here. A full description of the treatments is described in the study by Sennerstam et al [34].

### Outcomes

The primary outcome in this study and the original RCT is PSS-10 [35]. The PSS-10 is a self-report questionnaire developed to evaluate an individual’s perception of life as unpredictable, uncontrollable, and overwhelming. Responses are recorded on an ordinal scale ranging from 0 n*ever* to 4 *very often*, reflecting the individual’s feelings and thoughts over the past month. It contains statements, such as ‘*In the last month, how often have you been upset because of something that happened unexpectedly?’* and sum scores range from 0 to 40. The PSS is the most commonly used outcome measure of stress-management interventions globally [8,36,37]. For this study, a Swedish version of the PSS-10 was used. The PSS-10 has been found to exhibit high internal consistency (Cronbach α=0.84) and adequate construct validity [38]. The PSS-10 was administered digitally through the web-based study platform before randomization to treatment, every 3 weeks during the treatment phase, and at treatment completion (12 weeks). During treatment, the instructions for the PSS-10 were modified to have patients consider the last week instead of the last month. For this study, the sum score of the PSS-10 will be dichotomized into responder or nonresponder after treatment based on the RCI criteria [39] to differentiate between statistically significant change and those attributable to measurement error or natural variability. The PSS-10 baseline and 3-week measurement will also be used as predictors.

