When it comes to studies investigating predictors of treatment for stress-related disorders, Kocalevent et al [15] found that symptoms of anxiety but not perceived stress, depressive symptoms, or demographic variables predicted self-rated mental health following treatment for patients diagnosed with AD. In a study investigating burnout, Pallich et al [21] identified emotional competence, but not demographic characteristics, as a predictor of treatment response. However, both of these studies suffer from limited generalizability due to their inadequate description of the treatment offered, the fact that the interventions were conducted in an inpatient setting, and the lack of control groups. In ED patients, one study identified several predictors of treatment outcome following multimodal rehabilitation, including younger age, baseline symptom severity (insomnia, anxiety, and depression), perfectionism, physical activity level, treatment credibility, and a history of sickness absence due to ED [22]. However, the effects of demographics and pretreatment symptoms were so small that they offered limited clinical utility. In sum, at the current stage of research, it is a challenge for clinicians to determine who will benefit from treatment, underscoring the imperative for more sophisticated predictive studies.

Traditionally, prediction in psychiatry has relied on interpretable linear or logistic regression models. The aim has been to identify variables explaining a statistically significant portion of the variance in outcome, under the premise that such variables should inform researchers and clinicians. For example, the presence of previous sickness absence and earlier unsuccessful treatment attempts might lead a psychologist to conclude that a patient requires additional support, possibly extending the treatment duration. Although this approach of identifying predictors has offered some clinical utility, it often falls short in practice; the predictive power of specific variables in isolation is typically inadequate to inform assessment, treatment selection, and adaptations of interventions. Given the inherent complexity of mental disorders, the likelihood of pinpointing strong predictors with clinical utility is small, thus limiting the practical value of this approach [23,24].

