### Putative Predictors

#### Overview

Predictors were gathered through self-report measures that were administered in the web-based study platform, clinical assessment conducted before inclusion to the study, and remote cognitive testing. Table 1 presents all predictors included in the study.

**Table 1 table1:** Putative predictors of treatment outcome in stress-related disorders

Predictor		Construct measured	Type	Clinician-rated	Scoring range

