**3-week measurement**					
	SMBQ cognitive weariness	Burnout	Continuous		0-7
	SMBQ exhaustion	Burnout	Continuous		0-7
	SMBQ listlessness	Burnout	Continuous		0-7
	ISI	Insomnia severity	Interval		0-28
	PSS-10	Perceived stress	Interval		0-40

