#### Treatment-Related Predictors

*Clinician Treatment Expectancy* was judged after patient assessment, upon inclusion in the study, by clinicians rating the probability of the patient improving after treatment on a scale of 0 *no improvement* to 10 *full remission*.

The *Treatment Credibility Scale* was administered 3 weeks after the start of treatment [57]. Patients were asked questions about their impression of the treatment and if they thought they would improve. It included statements such as “How logical do you think this treatment is?” and “How confidently would you recommend this treatment to a friend with the same problems as you?” on a scale of 0 *not at all* to 10 *very logical*, *very confidently.*

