#### Data Cleaning and Preparation

We will transform categorical variables into a format suitable for numerical analysis. For binary categorical variables, we will use label encoding. For multinomial variables, we will apply one-hot encoding. In addition, for ordinal data, which have a natural order, we will transform the categories into integers.

Predictor variables with over 20% missing data will be excluded from the analysis. Categorical variables exhibiting low variance, as determined by predictors with <5% of a certain response will be removed. For instance, by removing the variable “Sleep medication” if it only occurs in 3 out of 300 patients. This approach aims to reduce unnecessary complexity in the predictions and to minimize the risk of overfitting. To control for multicollinearity, variables with a correlation coefficient ≥0.8 will be removed from the traditional prediction analysis but will be retained for the ML model development. Data that are highly skewed will be transformed if deemed appropriate.

Cognitive test results will be manually reviewed before model fitting to validate a proper result. Comments pertaining to technical difficulties and disturbances that may have affected the test result will be assessed by two of the authors and lead to exclusion if so judged. Participants who have noted during screening that Swedish is not their native language will be excluded from the analysis for CERAD and FAS. We will standardize the raw scores from the cognitive tests using normative regression models with age, education and sex as covariates. This standardization process will convert raw scores into *Z* scores, as previously described by Franke Foyen et al [62] and for a full overview of the multiple linear regression models used and how they were calculated, see the studies by Mindmore [77] and van den Hurk et al [78].

Patients who have missing data for the posttreatment PSS-10, ie, the missing outcome variable for the primary aim, will be replaced by a PSS-10 process measurement at week 10 if available; If not, the patient will be excluded from the analysis. The number of participants excluded from the final models will be described.

To prepare our primary outcome, RCI for the PSS-10 before to after treatment will be computed using the following formula [39]:

Cronbach α=0.83 from normative data will be used [38]. Patients exhibiting an RCI of −1.96 will be classified as responders.

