#### Predictor Analysis

For the traditional regression analysis, data will be imputed using the KNN imputer. The imputer, a nonparametric imputation method, works by imputing missing values based on the k-nearest neighbors; in this study *k* will be determined by cross-validation. It uses the Euclidean distance metric to find the nearest neighbors and can be used for both numerical and categorical data. Each missing value is imputed using values from its k-nearest neighbors. After imputation, we will run univariate logistic regressions for each predictor listed in Table 1 using RCI as a target variable. Predictors that are statistically significant in the univariate analyses will then be included in an ablation study, a systematic approach to evaluate feature importance. This method involves iteratively removing each significant predictor from a full model, measuring the change in explained variance, and then reinserting it, thereby quantifying each predictor’s unique contribution to the model’s explanatory power in the context of all other features.

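### Baseline and week-3 predictors form one set with no baseline-only model, and the univariate PSS-10 odds ratios are distorted by the change-based outcome

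*Protocol article*

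**What the plan says.** All references are to the protocol article.

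- **Predictor set.** Putative Predictors, Overview: "Table 1 presents all predictors included in the study". The table holds pre-treatment variables and a block headed "3-week measurement" with three SMBQ scales, ISI and PSS-10. Treatment credibility is listed outside that block, but Treatment-Related Predictors says it "was administered 3 weeks after the start of treatment". On PSS-10, Outcomes says "The PSS-10 baseline and 3-week measurement will also be used as predictors".
- **Outcome.** Data Cleaning and Preparation: "RCI for the PSS-10 before to after treatment will be computed using the following formula". Patients at the −1.96 cut "will be classified as responders".
- **Traditional analysis.** Predictor Analysis: "we will run univariate logistic regressions for each predictor listed in Table 1 using RCI as a target variable". Only predictors significant at that step go on to the multivariable ablation study. Data Cleaning and Preparation removes variables correlated at 0.8 or more from this analysis, without saying which of a pair goes, and keeps them for machine learning.
- **Benchmark.** Model Interpretation sets each classifier's test-set BACC against 67% as the mark of clinical usefulness.
- **Purpose.** The Background of the Introduction says "it is a challenge for clinicians to determine who will benefit from treatment". The Abstract speaks of better assessment procedures. Implications for Clinical Practice names therapy selection and also the following of progress during treatment.

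**The concern.** There are two linked problems.

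1. **Time of prediction.** A model that takes week-3 inputs can only be run after three weeks of treatment. If such a model reaches 67%, the reader cannot tell whether the outcome was predictable at assessment or whether the model read improvement already under way. The first would support claims about choosing treatment; the second would support claims about adjusting it.

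2. **Coupling with the outcome.** Baseline PSS-10 is one of the two scores from which response is computed. Its measurement error therefore appears on both sides of the univariate regression, with a sign that makes high scorers look like responders. Baseline symptom severity is a stated hypothesis, so part of its apparent support could be an artefact. Week-3 PSS-10, taken alone, reflects both where the patient started and how far the patient has moved. The two can offset each other, and a predictor that fails the univariate screen never reaches the ablation model.

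**Working it through.** **Step 1. Predictors by time.** Week 3: SMBQ (three scales), ISI, PSS-10 and treatment credibility, six in all. The rest of Table 1 is not placed in the 3-week block or dated to week 3.

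**Step 2. Uses set beside inputs.**

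| Use named in the article | Baseline-only model | Model with week-3 inputs |
|---|---|---|
| Assessment (Abstract) | yes | no |
| Therapy selection (Implications) | yes | no |
| Added support for likely non-responders (Background) | yes | yes |
| Monitoring during treatment (Implications) | no | yes |

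No baseline-only model is stated, so the first two rows have no matching BACC.

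**Step 3. Can the 67% verdict turn on week-3 data?** The article gives no PSS-10 correlations, so these are assumed: baseline/week 3 0.5–0.7, baseline/post 0.2–0.6, week 3/post 0.5–0.7, post SD 1.15 times baseline SD, 36–52% responders. Best-cut BACC, using PSS-10 only and a very large sample, was 0.60–0.69 with baseline alone and 0.68–0.75 with week 3 added. In five of the seven correlation sets baseline alone was below 0.67 (0.60–0.65) and the pair was above it (0.68–0.72).

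**Step 4. The response cut.** The equation is not legible in the text, so the usual form is assumed: RCI = (post − pre) / (SD × √(2(1 − α))). With the stated α = 0.83, the cut is a fall of 1.96 × √(2 × 0.17) = 1.14 baseline SDs, or 5.7, 6.9 or 8.0 points at an assumed SD of 5, 6 or 7.

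**Step 5. Baseline PSS-10.** In baseline-SD units let observed baseline b = T + e, with Var(T) = 0.83 and Var(e) = 0.17, and post = T + D + error. Then Cov(b, post − b) = Cov(T, D) − 0.17. If true change D is unrelated to true baseline T, the covariance is −0.17. Higher b goes with a larger fall although T has no effect.

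Simulation (assumed: n = 270, that is 300 less 10%; SD 6; SD of true change 4–7 points; about 40% responders): the odds ratio for true baseline was 1.00. For observed baseline it was 1.23–1.37 per SD, significant in 40–72% of studies. Separate runs over the same SDs differed at the edges, with low ends of 32–40% and high ends of 69–72%.

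If higher true baseline goes with less improvement at slope 0.2, the covariance is 0.2 × 0.83 − 0.17 = −0.004. The simulated odds ratio was then 0.99, significant in 4%. The upward push is still there; it now cancels a real association in the opposite direction.

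**Step 6. Week-3 PSS-10, unadjusted.** Under the Step 3 correlations, Cov(week 3, change) = 1.15 × r(week 3, post) − r(baseline, week 3).

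| r(base, wk 3) | r(base, post) | r(wk 3, post) | Covariance | OR alone | OR given baseline |
|---|---|---|---|---|---|
| 0.6 | 0.4 | 0.6 | 0.69 − 0.60 = 0.09 | 0.90 | 0.30–0.32 |
| 0.7 | 0.5 | 0.6 | 0.69 − 0.70 = −0.01 | 1.01 | 0.36 |
| 0.5 | 0.5 | 0.6 | 0.69 − 0.50 = 0.19 | 0.75 | 0.36 |

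Over all sets the odds ratio per SD was 0.75–1.05 alone and 0.27–0.45 with baseline in the model. In the Step 5 set-up, with 30% of true change present by week 3, it was 0.63–0.79 alone (power 43–98%) and 0.17–0.25 adjusted (power 100%).

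**Step 7. Is the adjusted figure the early-change effect?** No. Take no early change at all. The unadjusted covariance of week 3 with change is 0, but given baseline it is 0 − 0.83 × (−0.17) = +0.14, because week 3 helps to reveal the error in baseline. In simulation the odds ratio was 1.00 unadjusted but 0.50–0.63 adjusted, significant in 61–91% of studies.

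**The case against.** Several counter-arguments have force.

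- **A reader might infer that no analysis conditions on baseline PSS-10.** The article does not support that. Baseline PSS-10 is a listed predictor, so it is a candidate feature in all four classifiers, and correlated variables are kept there. It also enters the ablation model if it passes the screen and is not removed at 0.8. Only the univariate step is always unadjusted.
- **A reader might infer that nothing in the study can inform assessment.** That is too strong. Univariate results for pre-treatment variables are usable at assessment. A week-3 model fits the on-treatment uses that the article names, and the week-3 timing is stated openly. Nor are the week-3 variables certain to be used: the 20% missing-data rule, predictor selection in the training set and the elastic net could each drop some.
- **Adjusting every regression for baseline is not a clean cure.** Step 7 shows that it produces its own artefact for week-3 PSS-10. This stands and shapes the fix.
- **The severity hypothesis is broader than PSS-10.** The earlier exhaustion-disorder study summarised in the Background defines baseline severity by insomnia, anxiety and depression. Error specific to PSS-10 does not enter those scales, so the artefact concerns the single baseline PSS-10 odds ratio, not the whole hypothesis.
- **The magnitudes are illustrations.** The article gives no PSS-10 SD, correlations or responder rate.

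What remains is the missing baseline-only model, and the reading and screening of the two univariate PSS-10 odds ratios. Neither is a detail left for a fuller document: the article itself fixes one predictor table and unadjusted univariate screening.

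**Conclusion.** The point holds in this limited form. One predictor set mixes pre-treatment variables with six week-3 variables, and one BACC per classifier against 67% cannot separate prediction at assessment from prediction during treatment. This follows from the text and needs no assumption. That the 67% verdict can hinge on week-3 data rests on the assumed correlations of Step 3.

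In the traditional analysis, the upward push on the baseline PSS-10 odds ratio follows from the RCI definition and imperfect reliability. Its size does not: 1.23–1.37 per SD, significant in 40–72% of studies, applies when true change is unrelated to true baseline and has an SD of 4–7 points. Under a mild dependence of change on true baseline the observed association disappears. The unadjusted week-3 odds ratio was closer to 1 than the baseline-adjusted one in every scenario with a week-3 signal, so it may be lost at the screen. The gap between the two must not be read as a hidden early-change effect, since part of it is baseline measurement error.

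This should be changed before analysis. The article reports that the data had not been analysed for this study as of March 2025.

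**What to change.** 1. **Two predictor sets.** Fit each classifier on baseline variables only, for claims about assessment and therapy selection, and on baseline plus week 3, for claims about adapting treatment. Place treatment credibility in the second set. Report both BACCs against 67%, with their paired difference on the same test patients.
2. **Severity hypothesis.** Do not count the unadjusted baseline PSS-10 odds ratio as support. Test the hypothesis with the other baseline severity scales, with baseline PSS-10 as covariate. These scales share true stress with PSS-10, so their adjusted odds ratios can also carry some of its error; read them as predictive quantities.
3. **Week-3 PSS-10.** Keep baseline PSS-10 in any model that contains week-3 PSS-10, exempt from the significance screen and from removal at 0.8. The exemption matters: in the simulations with 30% early change the two scores correlated 0.75–0.77. State that the adjusted week-3 odds ratio partly reflects baseline measurement error and is not a pure early-change effect.

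Cost: twice the machine-learning runs and one covariate. No new data are needed.

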### Putative Predictors

#### Overview

Predictors were gathered through self-report measures that were administered in the web-based study platform, clinical assessment conducted before inclusion to the study, and remote cognitive testing. Table 1 presents all predictors included in the study.

**Table 1 table1:** Putative predictors of treatment outcome in stress-related disorders

Predictor		Construct measured	Type	Clinician-rated	Scoring range
**Sociodemographics**					
	Age (y)	—^a^	Interval		18-65
	Sex	—	Categorical		Male or female
	Relationship status	—	Categorical		3 categories
	Number of children	—	Interval		0-∞
	Educational attainment	—	Ordinal		9 categories
	Employment status	—	Categorical		8 categories
	Employment type	—	Categorical		11 categories
	Self-rated computer skills	—	Ordinal		5 categories
	Self-rated reading skills	—	Ordinal		5 categories
	Swedish native speaker	—	Categorical		Yes or no
**Clinical characteristics**					
	Number of medications	Medication	Interval	✓	0-4
	Antidepressants	Medication	Categorical	✓	Yes or no
	Sleep medication	Medication	Categorical	✓	Yes or no
	Pain medication	Medication	Categorical	✓	Yes or no
	Anxiolytics	Medication	Categorical	✓	Yes or no
	Diagnosis	Primary diagnosis	Categorical	✓	2 categories
	Secondary diagnosis	Secondary diagnosis	Interval	✓	0-4
	Depression	Secondary diagnosis	Categorical	✓	Yes or no
	Anxiety disorder	Secondary diagnosis	Categorical	✓	Yes or no
	Insomnia	Secondary diagnosis	Categorical	✓	Yes or no
	Other disorders	Secondary diagnosis	Categorical	✓	Yes or no
	S-ED^b^	Exhaustion disorder	Ordinal	✓	3 categories
	ADNM-8^c^ criteria	Adjustment disorder	Categorical	✓	Yes or no
	ADNM-8 number of stressors	Adjustment disorder	Interval	✓	0-11
	ADNM-8 stressors	Adjustment disorder	Categorical	✓	16 categories
	Duration of current episode	—	Interval	✓	0-∞
	Age of first episode (y)	—	Interval	✓	0-65
	Sick-leave status	Sickness absence	Interval		0%-100% 5 steps
	Sick-leave duration	Sickness absence	Ordinal		5 categories
